## Secondary objective

To measure efficacy of the polymer biomaterial nerve conduit to support nerve regeneration following transection of the sensory nerve of the hand.

## Protocol

### Study design

This study is a UK-based, prospective, single-centre, unblinded, phase I clinical trial of a novel nerve conduit device. The proposed study will register eligible participants to undergoing repair of a transection of a sensory nerve of the hand using a novel, synthetic nerve conduit polymer. All participants that receive the nerve conduit device will be followed for a period of 12 months post-surgery.

### Study setting

Eligible participants will be identified by the Principal Investigator and Co-Investigators within the Department of Burns, Plastics and Reconstructive Surgery at Manchester University NHS Foundation Trust (MFT) outpatient department and trauma database.

Participants deemed eligible for consideration and potential entry into the study (see
Table 1) will be provided with a verbal and written explanation of the study. The participant will be given at least 4 hours and ideally greater than 24 hours to consider participation. The minimum of 4 hours is stated because these are participants with traumatic injuries and will occasionally require or be offered an operation within this time period. After all queries have been addressed and the clinical team is confident that the participant understands the study and all it’s requirements, participants will be consented onto the study.

**Table 1. T1:** Eligibility criteria.

Inclusion criteria	Exclusion criteria
Provision of informed consent prior to any study specific procedures.	Concomitant injuries requiring surgical treatment from other specialists outwith the hand injury.
Traumatic injury/injuries to the hand with clinical suspicion of sensory nerve transection mandating surgical exploration.	Specified co-morbidities that would increase a participants risk of infection including diabetes, renal/liver disease, autoimmune diseases, primary or secondary immunocompromised participants (including immunosuppressive drugs or known disease resulting in suppressed immunity).
Male and females aged 18–80.	A stated hypersensitivity or allergy to the polymers PCL/PLA.
	Any other significant co-morbidity impacting on the risk of surgery (to be determined by the surgical team).
	Known to have participated in a clinical trial of an investigational agent or device in the previous 30 days.

## Consent

Written consent will be taken from potential participants by a member of the trial team who is suitably qualified and experienced, is good clinical practice (GCP)-trained and who has been delegated by the principal investigator to undertake this activity (this delegation will be clearly documented on the delegation log). If a participant is unable to sign the relevant consent form due to physical difficulties resulting from their clinical condition or pre-existing physical condition (e.g. visual difficulties or limb weakness), witnessed consent will be obtained.

During the consent process it will be made clear to the participant that they will remain in the trial should capacity be lost unless the decision to withdraw them is made by their representative, the research team, or by their clinical team. A model consent form, alongside the patient information sheet, is available as
*Extended data*
^24^.

## Intervention

Participants recruited onto the trial will be operated on by way of routine surgical procedures in an operating theatre at MFT. Local anaesthetic (e.g. 0.5% marcaine and 2% lignocaine ± adrenaline 1:200,000) will be administered as deemed appropriate by the surgeon; and a general anaesthetic will be administered by the anaesthetic team as determined by the clinical situation.

In standard operating theatre sterile conditions, the wound will be debrided and irrigated as necessary. The digital nerve will be examined under loupe or microscope magnification and a decision made as to the most appropriate surgery method. If the nerve gap is less than 5 mm and the stumps can be co-apted in a tension-free manner, then the nerve will be repaired primarily (end-to-end). If the nerve gap is greater than 20 mm it will be repaired with a nerve graft or as has been decided between the participant and the surgeon. In the instance of a nerve gap between 5 and 20 mm, the Polynerve biomaterial nerve conduit will be used. Three diameters of Polynerve will be available sterilised and packaged: 1.5 mm, 2 mm and 3 mm diameter. All Polynerve conduits are 22 mm in length and will be cut to fit the nerve gap allowing for tension-free epineural suturing of the proximal and distal nerve ends. The nerve will be sutured into the Polynerve conduit with an 9/0 Ethilon suture (Ethicon, UK).

Skin will be repaired with standard treatment of Ethilon suture (Ethicon, UK). The wound will be covered with standard treatment of a barrier dressing such as Mepitel (Mölnlycke Health Care, Sweden), and a secure gauze-based dressing overlying. If concomitant injuries exist such as tendon injuries, then the hand will be dressed using standard treatment including post-operative splinting.

All participants will receive antibiotics at induction of anaesthetic and for 1 week post-operatively. This will be co-amoxiclav 625 mg three times daily, or if penicillin allergic clarithromycin 500 mg twice daily. This is standard treatment following nerve graft surgery.

Standard post-surgical follow-up will be conducted 1 week and 2 weeks post-surgery, and additional follow up at 3 months, 6 months and 12 months post-surgery will be scheduled (
Figure 1 and
Table 2).

**Figure 1. f1:**
[figure not shown]
Participant timeline.

**Table 2. T2:** Schedule of assessments.

Assessment/Procedure	Screening / Baseline	Surgery	1 week	2 week	3 month	6 month	12 month
			± 1d	± 1d	± 7d	± 30d	± 30d
**Participant informed consent**	**X**	**X**					
**Inclusion criteria**	**X**						
**Exclusion criteria**	**X**						
**Medical and surgical history**	**X**						
**Demographics**	**X**						
**Concomitant medication**	**X**		X	X	X	**X**	**X**
**Safety reporting**	**X**		X	X	X	X	**X**
**Surgery**		**X** ^a^					
**Sensory outcome assessment**	**X**	**X** ^b^			**X**	**X**	**X**
**Ultrasound Examination**					**X**	**X**	**X**
**Wound examination**			**X**	**X**	**X**	**X**	**X**

^a^ In the event of repeat surgery, the 3-month, 6-month and 12-month follow-up visits will be performed from the date of the first surgery.

^b^ Sensory outcome assessment to be completed pre-operatively.

### Known and potential risks of study procedures

The potential risks to all participants undergoing sensory nerve repair include abnormal scar formation (hypertrophy/keloid), delayed wound healing, pain related to the wound site, neuroma formation, altered sensation of the skin around the wound (paraesthesia), no improvement in recovery of sensation, surgical site infection and bleeding requiring surgery (haematoma). Depending of the severity of these events some may require further surgery.

The additional potential risks to study participants receiving our polymer nerve conduit are persistent infection, allergy to the polymers PCL/PLA, local irritation and extrusion of the device. Some such risks may require surgical removal of the Polynerve device. These complications have not occurred in any animal studies conducted to date.

### Sample size

As this was a phase I study, primarily assessing safety of the device, a pragmatic decision on achievable recruitment numbers at a single centre who would be able to complete 12-months follow-up was made, and no formal power calculations were performed. The trial will recruit 17 participants over 12 months at an intended rate of approximately 1 to 2 participants per month. All participants fitting the eligibility criteria will be recruited.

### Data collection

***Primary outcome.*** The primary outcome is safety following implantation of the Polynerve device. Safety will be assessed based on assessment of the number and degree (based on the Clavien-Dindo classification of surgical complications
^25^) of adverse device effects (ADE) that may occur during the study period
^26^. In order to ensure all ADE are captured, all adverse events (AE) will be assessed and recorded by the P.I. or appropriate co-investigator deputized by the P.I., immediately upon notification to the study team. (A full out-of-hours AE reporting facility is made available to all trial participants following implantation of a study device.)

The investigator will assess causal relationship between the medical device under investigation and each AE.

All expected AE/ADEs of grade 3 or above, except infection of the wound any occurrences of grade 2 or above, will be recorded as a serious AE (SAE) or serious ADE (SADE). Appropriate SAE reporting procedures will be followed including sponsor, MHRA and REC reporting—this will be overseen by a Trial Management Group (TMG).

The following variables will be collected in the case report forms (CRFs) for each ADE:

ADE diagnosis/descriptionThe date of ADE onset and dateClavien-Dindo grade of maximum intensityWhether the ADE is serious or not (see above)Assessment of relatedness to device under investigation or other procedure.Outcome

Safety information and all concomitant medications (that are associated with the surgical procedure) will be reviewed at each follow up visit (
Table 2).

At the end of the study data from initial treatment will be combined in the presentation of safety data. The number of participants experiencing each ADE will be summarised. The number and percentage of participants with ADEs in different categories (e.g. causally related, Clavien–Dindo ≥3 etc) will be summarised by group. SAEs/SADEs will be summarised separately if a sufficient number occur. Any ADE occurring within the defined 12-month follow-up period will be included in the ADE summaries.

***Secondary outcome.*** To measure degree of efficacy of the nerve conduit device, standard sensory outcome measures will be used:

two-point discrimination (2PD)
^27^,the Weinstein Enhanced Sensory Test (WEST)
^28^,Locognosia test (adapted methodology from Jerosch-Herold
*et al.* JBJSB 2006)

These measurements will be assessed at baseline/time of surgery and at 3-, 6- and 12-months after implantation of the device (
Table 2). Data will be tabulated and appropriate statistical analysis performed.

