### Poly-lactic acid (PLA) and PCL

PLA and PCL are biocompatible and approved for use in numerous biomedical applications. Polylactide (L- and DL- forms) copolymerised with PCL have found utility in nerve guide conduits and Neurolac® (Polyganics, FDA 510 (k) 2003; CE mark 2004), consists of a poly (65/35(85/15 L/D) lactide ε-caprolactone) phospho-ester. Neurolac® has extensive pre-clinical
*in vivo* data, and in randomised clinical trials Neurolac® is reported to have comparable efficacy to gold standard autograft in defects up to 20 mm
^20^. Known adverse events associated with the use of a Neurolac® nerve guide include but are not limited to: failure to provide adequate nerve regeneration at sites where too much tension or compression occurs; failure to provide adequate/complete nerve regeneration; transitory local irritation; infection; allergy and delayed wound healing. Limitations are reported to be the high rigidity and inflexibility of the device. In comparison to Neurolac®, Polynerve has greater tensile strength, flexibility and less acidic degradation, whilst the microgrooves on the internal lumen provide a protected environment for ingress of Schwann cells (the supportive cell of the peripheral nervous system), which align on the micro-patterned grooves and aid subsequent nerve regeneration.

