### Harms

Expected AEs which may occur as a result of the surgical procedure include:

•   Bleeding from the wound site (haematoma)

•   Infection of the wound site

•   Abnormal scar formation (hypertrophy/keloid)

•   Delayed wound healing

•   Pain related to the wound site

•   Altered sensation of the skin around the surgical site (paraesthesia)

•   Development of neuroma

Expected ADEs which may occur as a result of the medical device under investigation are:

•   Intractable infection of the surgical site

•   Allergy to the polymers PCL/PLA

•   Local irritation

•   Extrusion of device through the wound

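### The primary safety summaries are defined on device-attributed events, so complications that an unblinded investigator judges surgical can be missing from the primary result

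*Protocol article*

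**What the plan says.** Under Data collection (Primary outcome), safety is assessed by the number and Clavien-Dindo degree "of adverse device effects (ADE) that may occur during the study period". All AEs are recorded so that no ADE is missed, and "The investigator will assess causal relationship between the medical device under investigation and each AE". AEs are thus the source, and ADEs are what remains after the causality judgement.

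The planned output follows the ADE definition. "The number of participants experiencing each ADE will be summarised", ADEs are counted by category, and those within 12 months are included. The case report form (CRF) variables, including grade, are also listed per ADE. Only one stated summary reaches events not attributed to the device: serious AEs and serious ADEs, which are summarised separately if their number is sufficient. That number is not defined.

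On design, the Study design section states: "This study is a UK-based, prospective, single-centre, unblinded, phase I clinical trial of a novel nerve conduit device". All implanted participants receive the same device.

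The Harms section has two lists. The one headed "Expected AEs which may occur as a result of the surgical procedure include" contains wound-site infection, delayed wound healing, scar formation, haematoma, pain, paraesthesia and neuroma. The device list contains intractable infection, polymer allergy, local irritation and extrusion.

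The section on poly-lactic acid and PCL gives known adverse events of an existing conduit, among them "failure to provide adequate/complete nerve regeneration; transitory local irritation; infection; allergy and delayed wound healing". The section on preclinical and clinical trials says that this conduit is made of similar polymer materials in a different ratio.

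**The concern.** In a single-arm, first-in-man device study nothing inside the trial shows whether a wound infection or slow healing is due to the operation or to the implant. The investigator must decide case by case, knowing that the device was used. If the primary summary contains only events that pass that decision, it depends on a judgement the reader cannot check, because the events that did not pass are not tabulated beside those that did.

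The error would run mainly one way. A device effect called surgical leaves the primary result, and the trial then looks safer than it was. The article's own account of the similar conduit shows that at least two events on the surgical list, infection and delayed healing, can plausibly be device effects.

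**Working it through.** **Step 1. Where each kind of event goes, as the text stands.** Data collection makes expected events serious from Clavien-Dindo grade 3, or from grade 2 for wound infection.

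| Event | Judged device-related | Judged surgical |
|---|---|---|
| Below the serious threshold | ADE summaries | Recorded; no stated summary |
| At or above the threshold | ADE summaries, and the serious-event summary if enough occur | Serious-event summary only, if enough occur |

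On the plain definition, no unconditional summary covers the right-hand column.

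**Step 2. Is the term used consistently?** Two phrases in the same section do not fit that definition. Causal relatedness is offered as an example of a category within ADEs, and the CRF records for each ADE its relatedness to the device or another procedure. If every ADE were already device-related, neither would be needed. The summarised set is therefore either device-related events only, with the gap above, or something wider that the definition does not say.

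**Step 3. How much attribution could matter.** There is no planned figure to reproduce: the Sample size section gives 17 participants and no power calculation, and no event rates are stated. The following is illustration, assuming that all 17 are implanted.

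Clopper-Pearson 95% intervals:

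- Lower limit: the 0.025 quantile of Beta(x, 17 − x + 1). Upper limit: the 0.975 quantile of Beta(x + 1, 17 − x).
- x = 0: 0% (0 to 19.5%).
- x = 1: 5.9% (0.1% to 28.7%).
- x = 3: 17.6% (3.8% to 43.4%).
- x = 5: 29.4% (10.3% to 56.0%).

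Each participant whose event is reattributed moves the rate by 1/17 = 5.9 percentage points.

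Chance that the primary result shows no event: let p be the assumed true rate of device-related complications and m the assumed share of them judged surgical. With independent participants, P(0) = (1 − p(1 − m))^17.

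| p | m = 0 | m = 0.5 | m = 0.8 |
|---|---|---|---|
| 10% | 16.7% | 41.8% | 70.9% |
| 20% | 2.3% | 16.7% | 50.0% |
| 30% | 0.2% | 6.3% | 34.9% |

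For example, p = 20% and m = 0.5 gives (1 − 0.10)^17 = 0.167.

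**The case against.** The strongest reply is that ADE may have been meant more widely. The two phrases in step 2 suggest that the summarised set could include events not judged device-related, with the related ones as a subset. That would be close to the remedy proposed here. This stands as a reason not to say that surgical events will certainly be left out. It does not rescue the text, because the definition then says something other than what is intended.

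Several stronger readings are tempting, and the documents do not support them.

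- *The Harms lists decide attribution.* They name expected events and are not a rule. Causality is assessed for every AE, so an event on the surgical list can still be called a device effect.
- *All infection is assigned to surgery.* Intractable infection is on the device list, persistent infection is named as an additional device risk under Known and potential risks, and wound infection has the lower threshold for seriousness.
- *The similar conduit's record covers the whole surgical list.* It names infection and delayed healing, but not neuroma, pain or paraesthesia.
- *Failed sensory recovery drops out.* Two-point discrimination, WEST and locognosia are reported as secondary outcomes at 3, 6 and 12 months with no attribution step.
- *Ultrasound findings are lost because no outcome uses them.* An article may leave their use to the full protocol.
- *Events escape oversight.* All AEs are recorded, and an independent data monitoring committee reviews accruing data. That protects participants during the trial. No role in attribution is stated for it, and it does not change the reported primary result.

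A full protocol or analysis plan may add an all-AE table. The point concerns how the article defines its primary outcome, not the absence of a routine table.

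**Conclusion.** The point holds as a weakness in the definition of the primary safety outcome. As written, an event that the investigator judges surgical can be missing from the primary result, and no control arm or stated independent causality review would reveal it. For infection and delayed wound healing the article itself gives grounds to think a device effect possible. The inconsistent use of ADE adds a second, smaller problem: two analysts could tabulate different sets of events.

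The size of any bias cannot be estimated from the documents. A reader might take 0/17 against 3/17 as the expected distortion. It is not: the count of three is assumed, and zero requires every one of those events to be judged surgical. It shows only that at this sample size a few attribution decisions can change the headline. The change is worth making before the data are summarised; it does not call the design into question.

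**What to change.** - Make the primary safety summary all AEs after implantation, by type and Clavien-Dindo grade, regardless of attribution. Show investigator-attributed device-related events as a subset of the same table.
- Record the listed CRF variables, including grade and relatedness, for every AE.
- Report serious AEs and serious ADEs always, whatever their number.
- Use AE for any event and ADE only for those judged device-related, and reword the category example to match.

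No default rule counting uncertain events as device-related is needed, and the two Harms lists need not be merged. Once all events are shown with their attribution, readers can judge for themselves.

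The cost is extra tables from events already recorded, and possibly wider completion of the CRF variables. The drawback is a less favourable headline rate that includes some purely surgical complications; the device-related subset beside it keeps that in proportion.

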## Demographic data

Characteristics of the participants, including medical history and disease characteristics at baseline will be listed for each participant and summarised for the whole cohort.

### Data management

A paper-based data capture system will be used for data collection and query handling.

Completed CRFs submitted to the clinical trials unit will be entered onto a study database by the trial data manager. The study database is stored on a secure server with controlled access, regular back-up of data and an audit trail of changes made to the data.

### Statistical methods

Demographic data will be tabulated. All primary outcome data will be described and summarised. Secondary outcome measurement data will be tabulated and mean ± SD of static 2PD, WEST and Locognosia compared to contralateral control nerves will be presented with one-way ANOVA analysis between groups.

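### The one-way ANOVA named for the sensory outcomes treats measurements on the same participants as independent groups

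*Protocol article*

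**What the plan says.** Statistical methods in the protocol article names one inferential method for the whole trial. Means and SDs of the three sensory measures are "compared to contralateral control nerves will be presented with one-way ANOVA analysis between groups". The groups are not defined there.

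Elsewhere the article describes only one set of participants. Study design calls the trial a "prospective, single-centre, unblinded, phase I clinical trial of a novel nerve conduit device" and follows everyone who receives the device for 12 months. Demographic data has baseline characteristics "summarised for the whole cohort". The sensory measures are "assessed at baseline/time of surgery and at 3-, 6- and 12-months after implantation of the device". The secondary-outcome text under Data collection adds "Data will be tabulated and appropriate statistical analysis performed", which names no method. The safety text in the same section also uses an undefined grouping: adverse device effects in different categories "will be summarised by group".

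**The concern.** A one-way ANOVA assumes that every observation is independent of every other. It has no term for the participant. A contralateral nerve belongs to the same person as the repaired nerve, and later visits are repeat measurements on that person. With no parallel arm, whichever way the groups are read (hands or visits), they consist of the same people.

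This is not a detail left to the statistical analysis plan. The protocol fixes a method, and the method does not fit the data that the protocol collects. A plan that followed the sentence would inherit the error, and one that departed from it would contradict the protocol.

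At stake is the only stated test of the secondary efficacy objective. If measurements within a person are positively correlated, a direct comparison of hands or of visits has too large a standard error and loses power, and with 17 participants there is little to spare.

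**Working it through.** **The plan's own figures.** There is no power figure to reproduce. Sample size says that 17 was a pragmatic choice without a power calculation. 17 over 12 months is 1.4 per month, which agrees with the stated rate of 1 to 2 per month.

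**Inputs.** n = 17 comes from the protocol. Everything else is assumed, because the article gives no values: two-sided 5% level, normal data, between-hand correlation ρ of 0.3, 0.5 and 0.7, and an SD ratio (contralateral to repaired) of 1 or 0.3. The lower ratio allows for an intact nerve varying much less than a repaired one.

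**Standard error, one visit.** Let s₁ and s₂ be the SDs of the repaired and contralateral nerves.

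- ANOVA standard error: √[(s₁² + s₂²)/n], with 2(n − 1) = 32 degrees of freedom.
- True standard error of the mean difference: √[(s₁² + s₂² − 2ρs₁s₂)/n]. A paired analysis estimates this with n − 1 = 16 degrees of freedom.
- Ratio: √[(s₁² + s₂²)/(s₁² + s₂² − 2ρs₁s₂)], which is 1/√(1 − ρ) when s₁ = s₂.

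Example, equal SDs, ρ = 0.5: 1/√0.5 = 1.41. Example, s₂ = 0.3s₁, ρ = 0.5: √[1.09/(1.09 − 0.30)] = √(1.09/0.79) = 1.17.

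**Type I error and power, by simulation at n = 17.**

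| SD ratio | ρ | SE ratio | Actual type I error of ANOVA | Power for 0.7 repaired-nerve SD: ANOVA | Paired |
|---|---|---|---|---|---|
| 1 | 0.3 | 1.20 | 2.1% | 51% | 63% |
| 1 | 0.5 | 1.41 | 0.7% | 51% | 77% |
| 1 | 0.7 | 1.83 | 0.1% | 52% | 94% |
| 0.3 | 0.3 | 1.09 | just under 4% | 78% | 81% |
| 0.3 | 0.5 | 1.17 | 2.7% | 79% | 86% |
| 0.3 | 0.7 | 1.28 | 1.8% | 81% | 91% |

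Simulation runs differ by about 0.1 to 0.2 percentage points in type I error and about one point in power. The paired test holds its level at about 5% throughout.

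**If the groups are the four assessments.** With equal variances and the same correlation between every pair of visits, the actual type I error is about 1.3%, 0.3% and 0.02% at correlations 0.3, 0.5 and 0.7. The failure is of the same kind and in the same direction.

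**Boundary.** With equal SDs and zero correlation, the one-way ANOVA keeps its level (5.0%). With a negative correlation of −0.2 it would be 7.4%, so the test is conservative only if the correlation is positive.

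**The case against.** The strongest defence is one of proportion. The primary outcome is safety, and it is only described and summarised. The trial has no power calculation, and no success criterion or go/no-go rule rests on the ANOVA. The means and SDs promised in the same sentence are correct as descriptions whatever test follows. All of this stands, and it limits the severity.

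The size of the error also depends on inputs that the article does not give. If the contralateral nerve varies little, the loss is modest: 79% against 86% power at ρ = 0.5. If the correlation were zero, pairing would cost a little power (with equal SDs and a 0.8 SD difference, about 59% against 62%). That stands too, and it is why the result is given as a range.

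A reader might infer more than the text supports:

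- *Inflated false positives.* Stacking the post-operative visits within each hand can make the test anti-conservative, but nothing in the article says that visits will be pooled.
- *Several repaired nerves per participant.* The eligibility criterion, "Traumatic injury/injuries to the hand with clinical suspicion of sensory nerve transection mandating surgical exploration", refers to hand injuries. The article mentions tendon injuries as concomitant ones and speaks of the nerve repair in the singular.
- *Baseline ignored.* If the groups are visits, the pre-operative assessment is one of them. The sentence gives baseline no explicit role, which is a weaker statement. A transected nerve may also be near the floor of the scale.
- *Non-significance read as recovery.* No passage says that a non-significant difference will be taken this way.

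The promise of appropriate analysis under Data collection does not answer the core point, because it names no method and leaves the named test in place.

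**Conclusion.** The concern holds in a limited form and should be fixed. The named test does not suit a single cohort in which each participant supplies both sides of the comparison, and no available reading of the groups makes the observations independent by design.

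For repaired against contralateral nerve at one visit, under assumed correlations of 0.3 to 0.7, the standard error is 9% to 83% too large and the actual type I error lies between just under 4% and 0.1%. The practical harm is lost power and imprecise inference on the secondary objective, not a spurious claim of a difference. These figures rest on assumed normal data, correlations and SD ratios. Two-point discrimination, WEST and locognosia may be ordinal or bounded, so the exact values would change, but the lack of independence would not. The safety conclusions do not depend on this analysis.

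**What to change.** In Statistical methods, delete the reference to a one-way ANOVA between groups. In its place, state for each sensory measure:

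1. the within-participant difference, repaired minus contralateral, at each visit where both are measured, with a 95% confidence interval from a paired method;
2. the change from the pre-operative value to 12 months, also with a 95% confidence interval from a paired method.

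A repeated-measures or mixed model with participant as a random effect would serve equally well. The choice between parametric and rank-based paired methods can be left to the statistical analysis plan.

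The article does not say whether the contralateral nerve is tested at every visit, so the sentence should say at which visits it is. The undefined reference to groups in the safety summary can be cleared up in the same edit.

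The cost is one reworded sentence and trivial extra analysis work. Item 1 is limited to visits where both nerves are measured and item 2 uses assessments already scheduled, so neither needs new data.
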